### Randomisation

The participants will be randomised to either the PREVSAM model or to treatment as usual (TAU). Sequentially numbered, opaque, sealed envelopes containing notes marked ‘PREVSAM’ or ‘TAU’ are block-randomised by a computer programme in blocks of six (three of each), in order to ensure an even distribution. These are placed in a box at each participating centre. The allocation sequence will not be accessible to the persons who enrol participants and assign intervention. Enrolment and assignment of intervention will most often be done by a person from the interdisciplinary team.

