### Statistical analyses

Primary outcomes are sickness absence and sick days, where the first outcome is binary and the second one is continuous and most likely skewed [47]. Sick leave regardless of reason will be retrieved. However, sick leave for diseases of the musculoskeletal system and connective tissue is of specific interest. Sample size calculations will be based on the general assumptions that we want a power of 80% and that statistical significance is set to α = 0.05. For the outcome sickness absence, the difference between the proportion of sickness absence = yes/no will be compared between the intervention (PREVSAM model) and control (TAU) group. We assume that approximately 30% in the control group will have sickness absence = yes at least one time during the 12 month follow-up period [48]. If the percentage of sickness absence = yes in the intervention group is assumed to be 15% or 20%, then the sample size in each group needs to be 312 individuals and 132 individuals, respectively. To detect a difference of 15% (30% with sickness absence in control group and 15% with sickness absence in intervention group), a total sample size of 264 (132 individuals in each group) would give approximately 80 cases to analyse for the primary outcome sick days. This would enable us to estimate 8 parameters in a logistic regression analysis. This would mean a power of about 75% to detect a difference of at least 0.6 Ln (sick days), if the standard deviation for Ln (sick days) is assumed to be 1. This is equal to a scenario with mean sick days of about 35 in the intervention group (PREVSAM model) and 68 in the control group (TAU). This would enable us to perform linear regression analysis adjusting for several covariates and estimating about 7 parameters. To summarise these calculations and allowing for dropouts, randomisation of 200 individuals to each group is required. An interim analysis will be performed for the primary outcome when 50% of patients have been randomised and have completed the 12 months follow-up. At the same time-point it might be possible to perform the short-term follow-up analyses. The interim analysis will be performed by a statistician, blinded to the treatment allocation. The statistician will report and discuss the results of the interim analysis with the steering committee in a joint meeting. The steering committee decides on the continuation of the trial.

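### The two per-group sample sizes are attached to the wrong scenarios: 132 belongs to a 15% intervention rate and 312 to a 20% rate, not the reverse

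*Protocol article*

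**What the plan says.** The sample size is set out in the Statistical analyses section of the protocol article. The general settings are "we want a power of 80" percent and "statistical significance is set to α = 0.05". The control-group assumption is that "approximately 30% in the control group will have sickness absence = yes at least one time during the 12 month follow-up period".

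Two intervention rates are then considered. If the rate "is assumed to be 15% or 20%, then the sample size in each group needs to be 312 individuals and 132 individuals, respectively". Taken in order, 15% goes with 312 per group and 20% with 132 per group.

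The next sentence returns to the first scenario: "To detect a difference of 15% (30% with sickness absence in control group and 15% with sickness absence in intervention group"), for which it gives "a total sample size of 264 (132 individuals in each group").

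After a further calculation for the number of sick days, the section concludes that, with an allowance for dropouts, "randomisation of 200 individuals to each group is required".

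**The concern.** Adjacent sentences give the same scenario, 30% versus 15%, two different sizes: 312 per group and then 132 per group. The first pairing is also impossible on its face. With control rate, alpha and power held fixed, a 15-point difference cannot need more participants than a 10-point difference.

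What is at stake is how the final 200 per group is understood. A reader who relies on the first sentence sees 200 set against a stated need of 132 for 30% versus 20% and concludes that the trial is comfortably powered for a 10-point reduction. That would colour the reading of a null result. The section on ethical considerations already says that finding no benefit would clearly show the model need not be introduced early. That inference is weak for a 10-point effect if the trial has well under 80% power to see one.

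**Working it through.** **Inputs**, from Statistical analyses unless noted: control rate p1 = 0.30; intervention rate p2 = 0.15 or 0.20; power 80% (z = 0.8416); alpha 0.05; 1:1 allocation (Randomisation: "in blocks of six (three of each")). Neither sidedness nor the test is stated. I take a two-sided test (z = 1.9600) and report one-sided results as a check.

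**Formula**, per group, with p̄ = (p1 + p2)/2 and d = p1 − p2:

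n = [1.9600·√(2p̄(1−p̄)) + 0.8416·√(p1(1−p1) + p2(1−p2))]² / d²

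With continuity correction: n_c = (n/4)·[1 + √(1 + 4/(n·d))]²

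**30% versus 15%** (p̄ = 0.225, d = 0.15)
- n = [1.9600·√0.34875 + 0.8416·√0.3375]² / 0.0225 = (1.1575 + 0.4889)² / 0.0225 = 120.5, so 121
- n_c = (120.5/4)·[1 + √1.2214]² = 133.5, so 134

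**30% versus 20%** (p̄ = 0.25, d = 0.10)
- n = [1.9600·√0.375 + 0.8416·√0.37]² / 0.01 = (1.2002 + 0.5119)² / 0.01 = 293.2, so 294
- n_c = (293.2/4)·[1 + √1.1364]² = 312.8, so 313

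**Can the written pairing be reproduced?** No variant tried comes close.

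| Scenario | Written n | Two-sided | Two-sided, corrected | One-sided | One-sided, corrected | Unpooled | Arcsine |
|---|---|---|---|---|---|---|---|
| 30% vs 15% | 312 | 121 | 134 | 95 | 108 | 118 | 119 |
| 30% vs 20% | 132 | 294 | 313 | 231 | 251 | 290 | 292 |

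**Do the figures work when exchanged?** Yes. By exact binomial enumeration, the continuity-corrected two-sided test has 80.0% power at 132 per group for 30% versus 15%, and 80.0% at 312 per group for 30% versus 20%. Both numbers are sound; only their order is wrong.

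**Power, two-sided.** The uncorrected column uses Φ{[d·√n − 1.9600·√(2p̄(1−p̄))] / √(p1(1−p1) + p2(1−p2))}. The corrected column is by exact enumeration.

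| n per group | Scenario | Uncorrected | Corrected |
|---|---|---|---|
| 132 | 30% vs 20% (as written) | 46.6% | 41.4% |
| 312 | 30% vs 15% (as written) | 99.5% | 99.4% |
| 132 | 30% vs 15% (exchanged) | 83.5% | 80.0% |
| 312 | 30% vs 20% (exchanged) | 82.4% | 80.0% |
| 200, no losses | 30% vs 15% | 95.1% | 94.0% |
| 200, no losses | 30% vs 20% | 63.8% | 59.6% |

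For 200 per group and 30% versus 20%, for example: (0.10·√200 − 1.9600·0.6124)/0.6083 = 0.352, and Φ(0.352) = 0.638.

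**The case against.** The strongest reply is that this is a slip of order with no effect on the design. The very next sentence pairs 132 with 30% versus 15%, the sick-days calculation builds on that total of 264, and 200 per group is in line with 132 plus an allowance for dropouts. A literal reader would also have to conclude that 200 falls short of the 312 stated for 15%, so the sentence does not mislead in one direction only, and an attentive reader will notice that it cannot be right. All of this is fair, and it means the target of 200 need not be revisited. It does not make the sentence true: it misstates the size needed for a primary outcome, and correcting it changes what a reader should believe about a 10-point effect.

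A second reply is that 64% comes from an uncorrected test, whereas the protocol's 132 and 312 match a corrected one. That also stands in part. On the corrected basis the figure is about 60%, so 64% should be read as an upper bound for a two-sided test.

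A third is that 200 per group also summarises the sick-days calculation, so saying that the trial is sized only for a halving goes too far. I accept this and limit the statement to the yes/no outcome.

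**Conclusion.** The point holds. The two sample sizes are transposed: 132 per group is the requirement for 30% versus 15%, and 312 per group is the requirement for 30% versus 20%. The protocol's next sentence, the ordering of the effect sizes and the recalculation all agree.

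For the yes/no sickness absence outcome, 200 per group is adequate for a halving from 30% to 15%. For a fall from 30% to 20% it gives at most about 64% power (about 60% with continuity correction) before any dropout. If losses took the analysed number down to 132 per group, power would be 41% to 47%.

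These figures assume a two-sided test at 0.05 and 1:1 allocation. Two-sided testing with continuity correction is inferred, because it reproduces both stated numbers once they are exchanged. A one-sided test would give 75% for 30% versus 20% at 200 per group (uncorrected), still short of 80%, and would not reproduce either stated size. The error lies in the wording; the planned sample size is unaffected.

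**What to change.** Exchange the two numbers, so that intervention rates of 15% and 20% are matched to 132 and 312 per group in that order.

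Add one sentence: for the yes/no sickness absence outcome, 200 per group is sized for 30% versus 15% only and, with no losses, gives at most about 64% power for 30% versus 20% (about 60% with continuity correction). Naming the test and its sidedness there would put the sizes and the power on one stated basis.

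The cost is a sentence or two of text. Neither the recruitment target nor the analysis changes.

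### The 80 cases and 75% power quoted for sick days at 264 participants do not follow from the plan's own 30% and 15% rates, which give about 59 cases and about 58% power

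*Protocol article*

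**What the plan says.** All of this is in the protocol article, Statistical analyses. Sickness absence (yes/no) and number of sick days are both named as primary outcomes. The general settings are "we want a power of 80% and that statistical significance is set to α = 0.05".

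- **Control rate:** "We assume that approximately 30% in the control group will have sickness absence = yes at least one time during the 12 month follow-up period".
- **Scenario behind the case count:** "30% with sickness absence in control group and 15% with sickness absence in intervention group".
- **Resulting count:** "a total sample size of 264 (132 individuals in each group) would give approximately 80 cases to analyse for the primary outcome sick days".
- **Parameter budget:** "This would enable us to estimate 8 parameters in a logistic regression analysis". For the linear model of sick days the text gives about 7 parameters.
- **Power for sick days:** "This would mean a power of about 75% to detect a difference of at least 0.6 Ln (sick days").
- **Spread on which that power rests:** "if the standard deviation for Ln (sick days) is assumed to be 1".
- **Illustration of that difference:** "mean sick days of about 35 in the intervention group (PREVSAM model) and 68 in the control group (TAU").

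The text then arrives at 200 randomised per group after allowing for dropouts, without giving a dropout rate. The analysis description that follows restricts the sick-days comparison to participants with at least one spell.

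**The concern.** The case count is stated next to the two rates that should produce it, and it does not match them. Because sick days are compared only among people with a spell, the number of cases is the analysis sample for that outcome. An inflated count, with an implied equal split between arms, therefore carries straight into the power. It also carries into the number of covariates the models are said to support.

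The reader is told that one of the two primary outcomes has about 75% power at 264 participants. If the true figure is well below that, a null result on sick days would be read with more confidence than the design supports. Whoever chooses the adjustment covariates would also be working from too generous a budget.

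**Working it through.** **Inputs, all from Statistical analyses:** 132 per arm; absence 30% (usual treatment) and 15% (PREVSAM); difference 0.6 in Ln(sick days); SD 1; α = 0.05. Sidedness is not stated; two-sided is used here, with one-sided as a check.

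**1. Which rates belong to 132 per arm.** A two-proportion calculation for 30% against 15% at 80% power gives 121 per arm without continuity correction and 134 with it. So 132 belongs to the 30%/15% scenario, as the sentence says.

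**2. Reproducing the count of 80.** 264 × 0.30 = 79.2. The stated count appears when the control rate is applied to everyone.

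**3. Count from the stated rates.** 132 × 0.30 + 132 × 0.15 = 39.6 + 19.8 = 59.4, or about 40 and 20. With 20% in the intervention arm instead, 132 × 0.30 + 132 × 0.20 = 66, still well short of 80.

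**4. Power.** Two-sample t test, noncentrality = 0.6 / √(1/n₁ + 1/n₂), df = n₁ + n₂ − 2. For 40 and 40 the noncentrality is 0.6 × √20 = 2.68; for 40 and 20 it is 0.6 × √13.33 = 2.19.

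| Cases (usual treatment / PREVSAM) | What it represents | Two-sided power |
|---|---|---|
| 40 / 40 | 80 cases, equal split | 75.5% |
| 53 / 27 | 80 cases, 2:1 split as the rates imply | 70.8% |
| 40 / 26 | 264 participants at 30% and 20% | 65.0% |
| 40 / 20 | 264 participants at 30% and 15% | 57.7% |

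The stated 75% is the 40/40 row. That row assumes no effect on the yes/no outcome, in the scenario that assumes absence is halved. The normal approximation gives 76.5% for 40/40 and 59.1% for 40/20, so the choice of formula does not matter. One-sided testing gives 69.9% for 40/20 and 84.5% for 40/40, so neither split yields 75%.

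**5. Detectable difference.** With 40 and 20 cases, 75% power requires a difference of 0.73 rather than 0.6.

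**6. Parameter budget.** The plan's implied ratio for the logistic model is 80/8 = 10 cases per parameter; 59.4/10 gives about 6. For the linear model it is 80/7 = 11.4; 59.4/11.4 gives about 5.

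**7. At the number randomised.** The average rate is (0.30 + 0.15)/2 = 0.225, with cases split 2:1.

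| Analysed | Cases | Split | Power |
|---|---|---|---|
| 400 | 90 | 60 / 30 | 75.6% |
| 380 | 85.5 | 57 / 28.5 | 73.4% |
| 360 | 81 | 54 / 27 | 71.0% |
| 320 | 72 | 48 / 24 | 65.8% |
| 264 | 59.4 | 40 / 20 | 57.7% |

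**8. The illustrative means (minor).** ln(68/35) = 0.66, and 35 × e^0.6 = 63.8. The pair 35 and 68 therefore illustrates 0.66. Even at 0.66, 40 and 20 cases give 66% power.

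**The case against.** The strongest reply is that 264 is not the number to be randomised. With 400 randomised, power is 75.6% if nobody is lost and 71.0% at 10% loss. Loss on this outcome may be small: it comes from the social insurance register, participants consent to registry data, and those who withdraw are asked to allow continued registry collection. On this view the 58% describes a trial that loses 34% of its register data (1 − 264/400). The sample size is also driven by the yes/no outcome, not by this calculation.

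Much of that stands as a limit on the consequence. It does not make the text right: the 80 cases and the 75% are attached to 264, and 200 per arm is presented as that requirement plus a dropout allowance.

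Two further objections have force. The plan states no cases-per-parameter rule (10 is inferred from 80/8) and this section lists no covariates, so the lower count shows an overstated budget, not that any model will be overfitted. At about 356 analysed (80/0.225) there would be 80 cases and 8 parameters would fit that ratio. The mismatch between 0.6 and the means of 35 and 68 is softened by the approximate wording, and no design decision depends on it.

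**Conclusion.** The concern holds. On the plan's own rates, 264 participants give about 59 sick-day cases rather than about 80, and power for a 0.6 difference with SD 1 is about 58% rather than about 75%. The parameter budget falls from 8 to about 6 (logistic) and from about 7 to about 5 (linear) at the plan's own ratios. The cause that fits both stated figures is the control rate applied to both arms.

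The result assumes a two-sided 5% t test and expected case numbers of 40 and 20. Neither the normal approximation, one-sided testing nor the alternative 20% rate restores both stated figures. The 75% is reached only with essentially all 400 analysed. The number to randomise is not affected; what is wrong is the stated case count, power and covariate budget for a named primary outcome.

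**What to change.** Rewrite the sick-days part of the sample-size paragraph from the 30% and 15% rates:

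- At 264 analysed: about 59 cases (40 usual treatment, 20 PREVSAM), about 58% power for a 0.6 difference with SD 1, and about 6 parameters in the logistic model (about 5 in the linear model at the plan's own ratio).
- At 400 analysed: 90 cases (60 and 30) and about 76% power. Show at least one value between, such as 360 analysed (81 cases, 71%), so that the 75% is not read as surviving dropout.
- State that the test is two-sided, if that is intended, and that the case split is unequal.
- Give the illustrative means as about 35 and 64, or restate the difference as 0.66.

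In the same edit, correct the earlier sentence that pairs 15% with 312 per group and 20% with 132. The pairing is reversed: with continuity correction, 15% needs 134 and 20% needs 313.

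The cost is wording only. Enrolment, outcomes and tests stay as they are; the stated power for sick days becomes less favourable.

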### Blinding

Due to the nature of the intervention, neither participating healthcare professionals nor patients will be blinded to treatment. Investigators, outcome assessors and data analysts will be blinded to group allocation.

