Group characteristics will be presented as mean and standard deviations, median and 25th and 75th percentile or the number and percentage. For the primary outcomes descriptive analyses for sickness absence for the two groups will be presented according to recommendations [31]. The sickness absence will be presented with number of individuals who had sickness absence during the follow-up period. Proportions of individuals with sickness absence per month will be presented. The number of sick days (gross and net) with sickness benefit during the follow-up periods will be presented with mean and median values. For participation in work life additional measures will be presented with descriptive statistics regarding time to sick-leave spell for musculoskeletal pain. Number of days before a sick leave spell > 14 days occurs and number and duration of sick-leave spells per individual will be presented for gross and net days. Outcomes will be analysed according to intention-to-treat. Multivariable logistic regression analysis will be used for the primary outcome sickness absence during the follow-up period [1], not being sickness absent (0) adjusted for confounders. Multivariable linear regression analyses, or possibly quantile regression, will be used to evaluate differences between groups for sick leave days, among those have at least one sick leave spell. All other measurements will be analysed by calculating raw differences between baseline and follow-up assessments. Parametric and non-parametric tests will be used depending on data level and distribution. Sub-group analyses can be performed in regard to characteristics of interest, such as diagnosis or sick-leave. The level of significance is set to *p* < 0.05. Relevant statistical programs will be used for the statistical analyses, for example the IBM SPSS, SAS, STATA.

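### The interim analysis of the primary outcome has no stated stopping criterion while significance stays at 0.05, so a 5% type I error is not guaranteed

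*Protocol article*

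**What the plan says.** All of the interim plan stands in the Statistical analyses section of the protocol article.

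- Timing and outcome: "An interim analysis will be performed for the primary outcome when 50% of patients have been randomised and have completed the 12 months follow-up".
- Who does it: a statistician who does not know which arm is which.
- Who sees it: "The statistician will report and discuss the results of the interim analysis with the steering committee in a joint meeting".
- Who decides: "The steering committee decides on the continuation of the trial". No criterion is attached, and the decision is not limited to futility, safety or pooled data.
- Significance: for the sample size, "statistical significance is set to α = 0.05"; for the analyses, "The level of significance is set to *p* < 0.05". Neither statement makes allowance for the earlier look.

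Two other sections bear on this. Data collection says that there will be no data monitoring committee. Blinding says: "Investigators, outcome assessors and data analysts will be blinded to group allocation".

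**The concern.** An interim comparison of the primary outcome that can end the trial is a second chance to declare success. If the committee may stop on a favourable result and the final test still uses 0.05, the two chances together can exceed 5% under the null hypothesis. A reader of the final report could not tell by how much, because the rule for acting on the interim was never fixed.

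The interim is also not too early to produce a positive result. Under the protocol's own planning assumption it has a good chance of reaching nominal significance, so the question of what to do with such a result is likely to arise.

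The second matter is exposure. No independent body stands between the comparative results and those who decide on the trial. Patients and treating staff are unblinded, and short-term absence and the secondary questionnaires are self-reported, so knowledge of interim effects could matter.

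**Working it through.** **Inputs from Statistical analyses.** Alpha 0.05; power 80%; 30% with sickness absence in the control group; 15% (or 20%) in the intervention group; 132 per group for 15%; 200 per group randomised; one interim at 50%, so about 100 per arm and information fraction t = 0.5. Sidedness is not stated.

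**Step 1: reproduce the plan's sample size.** Arcsine formula with continuity correction, two-sided 0.05, 80% power:

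- h = 2·asin(√0.30) − 2·asin(√0.15); n = 2(1.960 + 0.842)²/h² = 118.55.
- Corrected: (n/4)·[1 + √(1 + 4/(n × 0.15))]² = 131.55, so 132.
- For 30% versus 20%: 291.69, corrected 311.37, so 312.

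Both planned sizes are reproduced exactly. (The sentence listing them pairs them the wrong way round; the next sentence gives 132 for 15%.) One-sided pooled calculations give 95 or 108 for 15%, and 231 or 251 for 20%, which do not match. The planned test is therefore taken as two-sided, and no allowance for an interim enters the planned size.

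**Step 2: type I error with two looks.** Under the null, the interim and final statistics Z₁ and Z₂ are bivariate normal with correlation √t = √0.5 = 0.707. If the trial may stop for benefit when |Z₁| > c₁ and is otherwise tested at 1.96,

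overall error = 1 − P(|Z₁| < c₁ and |Z₂| < 1.96).

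| Interim rule, final test at 0.05 | Overall two-sided error |
|---|---|
| stop for benefit at p < 0.05 | 8.31% |
| p < 0.02 | 6.09% |
| p < 0.01 | 5.46% |
| p < 0.005 | 5.19% |
| p < 0.001 | 5.02% |
| futility only, or pooled data | not above 5% |

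A simulation of 1,000,000 trials with a binary outcome, 30% in both arms, 100 per arm at the interim and 200 at the end, gave 8.4% for the first row. If the interim fell at t = 0.25 or 0.75, the first row would be 9.1% or 7.3%.

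**Step 3: is a nominally significant interim likely?** 30% versus 15% at 100 per arm, pooled z-test:

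- standard error under the null: √(2 × 0.225 × 0.775/100) = 0.0591
- standard error under the alternative: √((0.30 × 0.70 + 0.15 × 0.85)/100) = 0.0581
- (0.15 − 1.96 × 0.0591)/0.0581 = 0.59, so power is about 72%.

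**Step 4: boundaries that hold 5% at t = 0.5.**

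- O'Brien-Fleming: critical values 2.797 and 1.977, that is p < 0.0052 and p < 0.0480.
- Haybittle-Peto: p < 0.001 at the interim, p < 0.0498 at the end.

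**The case against.** The strongest reply is that the protocol does not say that the interim is tested at 0.05 or that the trial may stop for benefit. The p < 0.05 sentence is a general one, and an unseen SAP may hold a boundary. This stands as to size: 8.3% is the least favourable of the plausible rules, not a property of the plan. It does not remove the point. The article itself states the significance level, who discusses the results and who decides, and it limits the decision in no way.

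A second reply is that the interim statistician does not know the allocation. That does not affect the error rate, because a test of A against B is a test whatever the labels. It also gives limited protection once results by arm are discussed, since the trial's hypothesis is directional.

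Several stronger readings are tempting but not supported:

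- *The blinding statement is contradicted.* Results can be presented by coded arm, and the committee's membership is not given, so nothing shows that investigators would learn the allocation. Discussing results by arm weakens the blinding; it does not literally contradict it.
- *The two named primary outcomes multiply the error further.* That is a separate multiplicity question. The interim is described for one primary outcome, and any combined figure would need an assumption about the correlation between the outcomes.
- *Later recruitment would be affected.* With uniform accrual over R months, half the patients have completed 12 months at R/2 + 12 months. If R is 24 or less, everyone is already enrolled. The accrual period is not stated.
- *The short-term analyses make this worse.* The text says only "At the same time-point it might be possible to perform the short-term follow-up analyses". They concern secondary outcomes and add nothing to the error for the primary outcome.

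**Conclusion.** The point holds as a lack of guaranteed error control. With the interim, the committee's open discretion and the 0.05 level as stated, overall two-sided type I error lies between no inflation (futility-only or pooled look) and 8.3% (stop for benefit at p < 0.05). It is about 5.5% at an interim threshold of 0.01 and 5.02% at 0.001. These figures assume one interim at half the information, a two-sided test and a single binary primary outcome. A reader might infer that the plan does run at 8.3%; the text does not commit to the rule that would produce it.

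Discussing results by arm with a deciding committee, with no data monitoring committee in place, is a weakness in protecting the blinding rather than a breach of it. Both matters need to be settled before the interim, because a rule chosen after results are seen cannot restore the error rate credibly.

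**What to change.** Add one paragraph to the protocol or SAP before the interim is run, choosing one of two options:

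1. The interim is for non-binding futility only; the trial will not be stopped for efficacy; the final test stays at 0.05.
2. The interim tests one primary outcome, sickness absence yes/no, against a stated boundary: O'Brien-Fleming (p < 0.0052 interim, p < 0.048 final) or Haybittle-Peto (p < 0.001 interim, about 0.05 final).

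Under either option the statistician passes only *continue* or *boundary crossed* to the steering committee (under option 1, the boundary is the futility criterion). If an SAP already contains such a rule, the protocol should refer to it and the sentence about discussing results should be brought into line.

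The cost is small. With O'Brien-Fleming, power at the final level for 30% versus 15% moves from 95.1% to 95.0% at 200 per arm, and from 83.5% to 83.1% at 132 per arm. The required size rises by about one patient per group (121 to 122, or 134 to 135 with continuity correction). The committee gives up seeing interim estimates.
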